### Ethical standards

2.9

The ethical principles of the Declaration of Helsinki will be followed. The research proposal was formally submitted to the Ethics Committee for Research Involving Humans of the State University of Santa Catarina and received approval under number 5.729.066 (CAAE: 60046022.5.0000.0118). Additionally, the clinical trial was submitted and approved (RBR-9hk6pgz) by the Brazilian Registry of Clinical Trials (ReBEC). Prospective subjects who meet the eligibility criteria will be invited to participate in the study. Upon agreement, participants will start the interventions only after they had thoroughly read and signed the informed consent form.

### Data analysis

2.10

The data will be organized using Microsoft Excel and subjected to statistical analysis using the IBM SPSS 20.0 software. Descriptive statistics will be employed to assess all variables and will include absolute frequency, relative frequency, mean, and standard deviation. Data distribution normality will be tested by the Shapiro–Wilk test. Baseline characteristics will be examined based on the nature of the variables (numerical or categorical). Differences between groups at baseline will be evaluated using one-way analysis of variance (ANOVA) or the Kruskal-Wallis test for numerical variables and Pearson’s chi-square or Fisher’s exact test for categorical variables.

Repeated-measures ANOVA will be applied to assess post-intervention group-by-time interactions. Multiple comparisons will be performed using Tukey’s post-hoc test. Furthermore, potential associations between deltas (Δ) – mean changes before and after the intervention – of OSA-related outcomes (AHI and ODI) and possible explanatory variables (VO_2_, BMI, and NC) will be explored using Pearson’s or Spearman’s correlation test, depending on data normality. A 95% confidence interval will be employed in all analyses, corresponding to a significance level of 0.05 (5%). As highlighted previously, losses after randomization will be included in the intention-to-treat analysis but not in the analysis of the protocol. (Supplementary Table S1) shows the summary of the outcomes along with their respective measurement tool.

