### Sample size

2.3

To determine the minimum number of participants required for the interventions, the sample size was calculated using the GPower 3.1 software. Using repeated measures ANOVA (within-subjects and between-subjects interaction) and assuming a significance level (α) of 0.05, power (β) of 0.95, and effect size of 0.35 (da Silva et al., 2022), the minimum sample size is 30 individuals. This number will be increased by 20% to account for potential sample losses, resulting in a minimum sample size of 36 participants divided into two groups: – the exercise group (EG) and the control group (CG), each consisting of 18 subjects. Losses after randomization will be included in the intention-to-treat analysis but not in the analysis of the protocol.

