### Data collection

2.7

Before the recruitment process, participants will receive an explanation of the objectives and assessment procedures of the study. Upon agreeing to participate, the older adults will read and sign the informed consent form. Participants will then respond to the questionnaires and undergo HPSG to determine their eligibility for the study. After confirmation of their eligibility, older adults will complete the remaining questionnaires and undergo the remaining tests. Assessments regarding HPSG will be conducted by an assessor blind to treatment allocation. Because of the inherent characteristics of the intervention, it is not possible to maintain blinding for either the participants or the researcher regarding allocation. However, both are strongly advised against revealing the allocation status of participants during follow-up assessments.

Next, participants will be randomized to two groups: the exercise group (EG) and the control group (CG). To ensure similarity in participant characteristics within the groups, stratified randomization will be conducted to control the covariates sex (2 levels: male and female) and OSA severity (2 levels: moderate and severe). For this purpose, an external researcher will generate a computerized sequence of random numbers to determine the 1:1 allocation to either EG or CG based on the order of participant recruitment. The specific schedules for instrument administration and the data collection procedure are outlined in Figure 3.

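### An avoidable loss of precision: the planned group-by-time ANOVA is valid, but less efficient than an ANCOVA on baseline and the randomisation strata

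*Protocol article*

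**What the plan says.** Section 2.10 (Data analysis) names one comparative method: "Repeated-measures ANOVA will be applied to assess post-intervention group-by-time interactions". Tukey's test follows for multiple comparisons. No covariate is listed, neither the baseline value nor a stratification factor.

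Section 2.7 (Data collection) says that "stratified randomization will be conducted to control the covariates sex (2 levels: male and female) and OSA severity (2 levels: moderate and severe", and that a computer-generated sequence will "determine the 1:1 allocation to either EG or CG". Neither factor returns in section 2.10.

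Section 2.3 (Sample size) sizes the trial on the same test: "Using repeated measures ANOVA (within-subjects and between-subjects interaction". Its inputs are stated as "assuming a significance level (α) of 0.05, power (β) of 0.95, and effect size of 0.35". The result is that "the minimum sample size is 30 individuals". An allowance for dropout follows: "This number will be increased by 20% to account for potential sample losses". The final figure is 36, in two arms of 18.

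Section 2.6.2 (Physical fitness) separately bases the Senior Fitness Test results on the pre-post difference. Sections 2.3 and 2.10 both say that losses after randomisation enter the intention-to-treat analysis.

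**The concern.** With two arms and two time points, the group-by-time F test is the square of the t-test on change scores. A change score does use the baseline, but with a slope fixed at 1. ANCOVA estimates the slope. When the pre-post correlation is below 1 and the variances are equal, a slope of 1 is too steep. The change score then overcorrects for chance baseline differences between arms, which are to be expected with 18 per arm.

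Randomisation balances sex and OSA severity by design, but the analysis model does not carry them. Where they predict change, their variation stays in the residual error.

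What is at stake is the width of the confidence interval, and power for effects smaller than the one planned for. The trial is small, and the information needed for the better model is already collected.

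**Working it through.** **Inputs from the article.** Two arms, 1:1; alpha 0.05; power 0.95; f = 0.35; N = 30, raised to 36; strata sex (2 levels) and OSA severity (2 levels).

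**Assumptions.** Two time points: the schedule figures are not shown, but sections 2.6.2 and 2.10 speak of before and after. Equal variances at both times. The pre-post correlation rho is not stated, so a range is shown.

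**Step 1: reproduce the plan's figure.** For the interaction test, the noncentrality is lambda = f² × N × m/(1 − rho), with m = 2 time points and 1 and N − 2 degrees of freedom. At rho = 0.5 and N = 30, lambda = 0.1225 × 30 × 2/0.5 = 14.7 and power is 0.959. N = 28 gives 0.946. So 30 is reproduced at rho = 0.5, and 30 × 1.2 = 36.

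**Step 2: put the effect in SD units.** For a between-arm difference in change of D SD, the change-score noncentrality is N × D²/(8(1 − rho)). Setting this equal to Step 1 gives D² = 16f², so D = 4 × 0.35 = 1.4 SD.

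**Step 3: compare the two analyses.** The variance of the treatment effect is proportional to 2(1 − rho) for change scores and to 1 − rho² for ANCOVA. The ratio is (1 − rho²)/(2(1 − rho)) = (1 + rho)/2. The confidence interval narrows by 1 − √ratio.

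**Step 4: power at N = 36 and D = 0.8 SD.** This effect is illustrative and does not come from the article. The change-score noncentrality is 36 × 0.64/(8(1 − rho)) on 34 df. The ANCOVA noncentrality is 36 × 0.64/(4(1 − rho²)) on 31 df, which pays for baseline and both strata.

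| rho | Variance ratio | CI narrower by | Power, planned test | Power, ANCOVA |
|---|---|---|---|---|
| 0.3 | 0.65 | 19% | 0.50 | 0.68 |
| 0.5 | 0.75 | 13% | 0.65 | 0.77 |
| 0.7 | 0.85 | 8% | 0.85 | 0.90 |
| 0.8 | 0.90 | 5% | 0.96 | 0.97 |

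If losses leave 30 participants, the pair at rho 0.5 is 0.56 and 0.68.

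**Step 5: the plan's own effect.** At D = 1.4, N = 30 and rho = 0.5, the ANCOVA noncentrality is 30 × 1.96/(4 × 0.75) = 19.6 on 25 df. Power is 0.989, against 0.959 for the planned test. The N needed for 95% power is 24 instead of 30.

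**Step 6: what the strata add.** The formulas above ignore the small cost of estimating the baseline slope, so the models were also simulated with stratified 1:1 allocation (N = 36, rho 0.5, effect 0.9 SD, 8,000 runs).

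| Strata effect on follow-up | Planned test | Baseline only | Baseline and strata |
|---|---|---|---|
| None | 76% | 86% | 85% |
| 0.5 SD for each stratum | 69% | 79% | 84% |

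With no treatment effect and prognostic strata, the planned test rejected in about 4.0% of runs. The model with strata rejected in 5.3%.

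**The case against.** The strongest reply is that nothing here is an error. In a randomised trial the group-by-time test is valid and unbiased, and it agrees with the sample-size method in section 2.3. A covariate list may also stand in an analysis plan that is not shown. All of this stands. It limits the point to efficiency, but it does not remove it, because the article itself fixes the less efficient model.

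The second reply is that the loss is small where the plan expects to be: power is above 0.95 either way at 1.4 SD. That also stands for power. The confidence interval is still about 13% wider than it need be, relative to the planned width, at rho 0.5 whatever the effect, and power suffers if the true effect is smaller. If rho is 0.8, little is lost.

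The strata part is the weaker half. A stable stratum effect cancels in a change score, and for AHI the severity stratum largely duplicates the baseline value.

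A replacement ANCOVA would drop participants without a week-12 value. Repeated-measures ANOVA drops them too, so this does not favour the planned test, but the fix should deal with it.

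A reader might infer that the planned analysis is biased, that it ignores baseline, or that omitting the strata inflates the type I error. The article supports none of these: baseline enters through the change score, and omitting prognostic strata makes the test slightly conservative.

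**Conclusion.** The point holds as an improvement in precision at almost no cost, not as a matter of validity. Under equal variances and two time points, ANCOVA has 65% to 90% of the planned variance for rho between 0.3 and 0.8. The power gain ranges from 18 points to about 1 point at 0.8 SD with N = 36, and is 3 points at the plan's own effect with N = 30 and rho 0.5.

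A reader might conclude that the plan costs the trial one third of its participants. That figure is the large-sample ratio 1/0.75 at rho 0.5. At the design point the comparison is 30 against 24, or 25% more, and it shrinks as rho rises. Baseline adjustment carries most of the gain. The strata add precision only where they predict outcome beyond baseline.

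**What to change.** In section 2.10, make the primary comparison for each continuous outcome, PSQI and ESS first, an ANCOVA of the week-12 value on arm, baseline value, sex and OSA-severity stratum. An equivalent baseline-adjusted mixed model would also keep participants with partial data, in line with the stated intention-to-treat analysis. Report the adjusted between-arm difference with its 95% confidence interval. Keep the repeated-measures ANOVA as a sensitivity analysis.

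Align the Senior Fitness Test wording in section 2.6.2, and note in section 2.3 that the sample size was derived for the interaction test. Settle the choice before outcome data are seen, so that the adjustment cannot look data-driven.

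The cost is 1 degree of freedom for baseline and 2 for the strata, plus minor text edits. No new data are needed.

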### Primary outcomes

2.5

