#### Sleep quality

2.5.1

The Pittsburgh Sleep Quality Index (PSQI) (Buysse et al., 1989) will be used to evaluate sleep quality. The PSQI has been validated for use in Brazil (Bertolazi et al., 2011), showing high internal consistency (Cronbach’s α = 0.82). The questionnaire consists of 19 items that assess various sleep-related issues over the past month. The questions are divided into seven components and a score ranging from 0 to 3 is assigned to each component. These components include sleep quality, sleep duration, sleep latency, habitual sleep efficiency, sleep disturbances, medication use, and daytime dysfunction. The sum of scores for each component provides a global score ranging from 0 to 21, with higher scores reflecting poorer sleep quality. A score above 5 indicates poor quality (Buysse et al., 1989).

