#### Daytime sleepiness

2.5.2

Daytime sleepiness will be assessed with the Epworth Sleepiness Scale (ESS) (Johns, 1991). The instrument has been validated for use in Brazil, with a reliability coefficient of 0.83 (Bertolazi et al., 2009). The ESS is aimed at evaluating the likelihood of dozing off in eight situations known to induce sleepiness. Respondents are required to indicate the probability of falling asleep in each situation, which ranges from “would never doze” (0) to “high chance of dozing” (3). The overall score ranges from 0 to 24 and a score above 10 suggests a diagnosis of excessive daytime sleepiness (Johns, 1991).

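### Two primary outcomes are each tested at 0.05 with no rule across them, and Tukey's test, the only multiplicity tool named, does not address this

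*Protocol article*

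**What the plan says.** Section 2.5 of the protocol article carries a plural heading, "Primary outcomes". Two instruments stand under it. The PSQI "will be used to evaluate sleep quality" (2.5.1), and the ESS measures daytime sleepiness (2.5.2). Neither is ranked above the other.

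Section 2.10 (Data analysis) plans a repeated-measures ANOVA for the group-by-time interaction. It then says "Multiple comparisons will be performed using Tukey’s post-hoc test", without saying which means are to be compared. The level is set for everything at once: "A 95% confidence interval will be employed in all analyses, corresponding to a significance level of 0.05 (5"%).

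Section 2.3 (Sample size) rests on one interaction test, "assuming a significance level (α) of 0.05" and "power (β) of 0.95" (the 0.95 is read here as power), with effect size 0.35. It gives 30 participants, raised to 36. The outcome behind the effect size is not named.

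The trial has two arms (2.1 and 2.7).

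**The concern.** With two primary outcomes, a protocol has to say what counts as success: either one, both, or one before the other. This one does not. Because 0.05 is fixed for all analyses, each primary is tested at the full level. A reader of the eventual report could not tell whether one significant questionnaire out of two supports the trial's main claim. If it does, the 5% protection holds for each test but not for the claim.

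The Tukey sentence may give the impression that multiplicity has been dealt with. Tukey's procedure compares several means of a single outcome. It carries no information from PSQI to ESS, so it cannot limit the error across them.

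**Working it through.** **Inputs from the protocol article.** Two primaries (2.5); level 0.05 for each analysis (2.10); two groups (2.1, 2.7); effect size 0.35, power 0.95, N = 30, raised to 36 (2.3).

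**Assumed or inferred.**
- Effect size 0.35 is read as Cohen's f and taken to apply to each questionnaire.
- The before-after correlation within a person is taken as 0.5, since the article gives none.
- Two time points are inferred from the before and after changes in 2.10, since the schedule figures are not shown.

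**1. The plan's own figure.** For the interaction with two groups and two times, the noncentrality is f² × N × 2 / (1 − ρ), on 1 and N − 2 degrees of freedom. With N = 30 and ρ = 0.5 this is 0.1225 × 30 × 2 / 0.5 = 14.7, and power is 0.959. N = 28 gives 0.946, so 30 is reproduced as the smallest even total reaching 0.95. The result depends on ρ: N would be 56 at ρ = 0, 40 at 0.3 and 20 at 0.7.

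**2. Error across the two primaries if either counts.** For independent tests it is 1 − 0.95² = 0.0975. For correlated tests it is 1 − P(|Z₁| < 1.96 and |Z₂| < 1.96) under a bivariate normal. The correlation here is between the two test statistics and is not the ρ of step 1.

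| Test correlation | Chance of at least one false positive |
|---|---|
| 0 | 0.0975 |
| 0.3 | 0.095 |
| 0.5 | 0.091 |
| 0.7 | 0.083 |
| 0.9 | 0.070 |

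It exceeds 0.05 at every correlation below 1.

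**3. What Tukey does here.** The Tukey critical value on the t scale is the studentized range quantile divided by √2.
- Two means: 2.048 at 28 degrees of freedom and 2.032 at 34. These equal the unadjusted t values, so nothing is adjusted.
- Four group-by-time cells with a single error term: 2.730 at 28 degrees of freedom. This is a real adjustment, but within one outcome.

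On neither reading does it act across PSQI and ESS.

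**4. Cost of Holm.** Holm compares the smaller p value with 0.05 / 2 = 0.025 and, if that succeeds, the larger with 0.05. Power per outcome is therefore no lower than at 0.025, which is 0.922 with 30 analysed and 0.964 with 36 (ρ = 0.5). Holding 0.95 at 0.025 with the analysed number would need N = 34. By the plan's own loss allowance that is 34 × 1.2 = 40.8, so 41, or 42 for equal groups.

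**5. Cost of requiring both.** There is no inflation. With 0.95 per outcome, joint power is about 0.95² = 0.9025 if the tests are independent, and at most 0.95. Using the reproduced 0.959 it is 0.959² = 0.920.

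**The case against.** The strongest reply has four parts.

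**The article promises no 5% rate across outcomes.** This stands. The 0.05 is a level per analysis and is valid as such. A reader might infer that a stated error rate has been broken or doubled. The text supports only that the error over the pair is unprotected, and near-doubling is the upper end, reached only as the tests approach independence. PSQI has a daytime dysfunction component (2.5.1) that plausibly overlaps with sleepiness, so some correlation is likely.

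**No either-one rule is printed.** This also stands, and the 7% to 9.75% is conditional on that rule. The hypothesis in the Introduction speaks of reducing severity and symptoms together, which leans towards joint success. But it is not a decision rule for PSQI and ESS, and severity as measured by AHI is not listed in 2.5. If joint success is meant, the power statement needs changing instead.

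**Tukey can be used.** Correct. A reader might think it is impossible with two groups, but it is merely redundant there, and it is computable over the four cells.

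**Multiplicity may be left to an analysis plan.** This would answer mere silence. Here the article fixes 0.05 for all analyses and names a method. An analysis plan that applied Holm or dropped Tukey would contradict it.

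**Conclusion.** The point holds in this form: two primaries, each at 0.05, with no order, adjustment or success rule, and a named multiplicity method that does not act across outcomes. If either result may carry the primary claim, the false-positive chance is 9.75% with independent tests, falling to about 7% at test correlation 0.9. The article gives no correlation, so the range is the result. If both must succeed there is no inflation, but the stated power then does not describe the claim.

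Two further inferences are not supported. Counting AHI as a third primary would raise the figure to 1 − 0.95³ = 14.3% under independence, but section 2.5 does not list AHI; its status is a separate question. Regression to the mean after selection on high AHI concerns change in AHI within an arm. There is no entry threshold on PSQI or ESS, and the planned test is the group-by-time interaction, which is the randomised comparison.

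**What to change.** In section 2.10:
- Delete the Tukey sentence.
- State that the confirmatory test for each primary outcome is the between-group difference in change (the group-by-time interaction).
- Apply Holm to PSQI and ESS at an overall two-sided 0.05. Alternatively, state that both must be significant at 0.05.
- Limit the sentence that sets 0.05 for all analyses so that it agrees with the rule chosen.

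In section 2.3, restate the power under that rule. Under Holm, the strictest step gives about 0.92 with 30 analysed and 0.96 with 36, against the stated 0.95. Under joint success it is about 0.90 if each test has 0.95 and the tests are independent. The two Holm figures assume f = 0.35 for both outcomes and a before-after correlation of 0.5.

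The cost is wording and a small loss of power. No extra participants are needed unless the sponsor wants 0.95 per outcome at 0.025, which takes 34 before losses instead of 30.

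AHI should not be placed first in a testing order as part of this change. That would redefine the primary outcome and could block a claim on both listed primaries.

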#### Body composition

2.6.5

Anthropometric and body composition measurements will be carried out to examine various outcomes. These measurements will be used to determine possible correlations with changes in the primary outcomes of OSA after the intervention. Body weight will be measured with a G-Life^®^ Millenium digital scale (silver model CA6000). Height will be measured with a Cardiomed^®^ stadiometer (height limit of 2.16 m) from the feet to the highest point of the head. The body mass index (BMI) will be calculated from the body weight and height using the formula: BMI (kg/m^2^) = body weight (kg)/height^2^ (m). Neck circumference (NC) will be measured with a Cescorf^®^ measuring tape immediately above the thyroid cartilage.

Body composition will also be evaluated by whole-body dual-energy X-ray absorptiometry (DXA) using a Hologic system (Discovery Wi Fan-Beam, Bedford, Massachusetts, United States). The equipment will be calibrated daily and weekly according to the manufacturer’s recommendations. The same lab technician will position the participant for each scan, perform the scans, and analyze the data according to the operator’s manual using the standard analysis protocol. DXA provides data on bone mineral content (g), bone mineral density (g/cm^2^), lean mass (kg), and fat mass (kg).

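### The planned correlations of change in AHI and ODI with change in VO2, BMI and neck circumference do not say how treatment arm is handled; if the arms are pooled, allocation alone can make them significant

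*Protocol article*

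**What the plan says.** Section 2.10 (Data analysis) plans to relate the pre-post changes "of OSA-related outcomes (AHI and ODI) and possible explanatory variables", the latter being VO2, BMI and neck circumference. On the method it says that these associations "will be explored using Pearson’s or Spearman’s correlation test, depending on data normality". With two outcomes and three explanatory variables, that is six pairs. The same section sets the 5% level for every analysis.

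Section 2.6.5 (Body composition) announces the same kind of analysis for the anthropometric and body composition measures: "These measurements will be used to determine possible correlations with changes in the primary outcomes of OSA after the intervention".

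Neither section says whether the correlations are run over both arms together, within each arm, in the exercise group only, or with adjustment for arm. In section 2.10, group enters only the baseline comparisons and the repeated-measures ANOVA.

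**The concern.** A bivariate correlation over two randomised arms mixes two sources of association: the one between participants within an arm, and the one created because the arm means differ on both variables. Only the first says whether participants whose fitness, BMI or neck size changed more also had a larger change in AHI. The second restates the treatment effects.

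The article expects exercise to move both sides of some pairs. The hypothesis at the end of the Introduction is that OSA severity will fall relative to control. Earlier, the Introduction cites meta-analyses in which exercise improved VO2max and BMI as well as AHI and ODI. So if the trial works as hoped, a pooled test could reach significance without any within-arm relation.

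The stake is interpretive. The Introduction calls the mechanisms only partly understood, and no other analysis described in the article relates the OSA changes to candidate explanatory variables. A significant pooled coefficient would be easy to read as more than it shows.

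**Working it through.** **Inputs from the article.** Section 2.3 bases the sample size on a repeated-measures ANOVA interaction with "significance level (α) of 0.05, power (β) of 0.95, and effect size of 0.35", giving 30 participants, raised by 20% to 36 (18 per arm). Section 2.10 gives the 0.05 level and the test.

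**Assumptions.** The tests are two-sided. The effect size is Cohen's f. The change scores are normal with equal variance in each arm. The delta in section 2.10 applies to the explanatory variables as well as to AHI and ODI. The article gives no between-arm shift for AHI, ODI, VO2, BMI or neck circumference, so a range is used.

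**Step 1: reproduce the plan's figure.** For 2 groups and 2 times, the noncentrality is λ = f² × N × 2/(1 − ρ), with 1 and N − 2 degrees of freedom. The pre-post correlation ρ is not stated. With ρ = 0.5, N = 28 gives power 0.946 and N = 30 gives 0.959, so the stated 30 is reproduced. With ρ = 0.3 the result would be 40, and with ρ = 0.7 it would be 20. The inflation is 30 × 1.2 = 36, as stated.

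**Step 2: put the planning effect on the scale of change.** At N = 30 and ρ = 0.5, λ = 0.35² × 30 × 2/0.5 = 14.7. For two equal arms λ = N × d²/4, where d is the between-arm difference in mean change in within-arm SD units. So d² = 4 × 14.7/30 = 1.96 and d = 1.4. This serves only as the top of the range, because section 2.3 does not tie the effect to any of the five variables.

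**Step 3: pooled correlation when the within-arm correlation is zero.** With 1:1 allocation and shifts d1 and d2,

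r = (d1 × d2/4) / √[(1 + d1²/4)(1 + d2²/4)].

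- 1.4 and 1.4: 0.49/1.49 = 0.329
- 1.0 and 1.0: 0.25/1.25 = 0.200
- 0.8 and 0.8: 0.16/1.16 = 0.138
- 0.5 and 0.5: 0.0625/1.0625 = 0.059

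The sign of r depends on the direction of each shift; a two-sided test ignores it. The 5% critical value is t/√(t² + N − 2). For N = 36 it is 2.032/√(2.032² + 34) = 0.329. For N = 30 it is 0.361.

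**Step 4: rejection rates.** These come from 40,000 simulated trials per setting, with zero within-arm association and the pooled Pearson test at two-sided 0.05.

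| Shifts (SD of change) | r | N = 30 | N = 36 |
|---|---|---|---|
| 1.4 and 0 | 0.00 | 5.0% | 5.0% |
| 0.5 and 0.5 | 0.06 | 5.9% | 6.4% |
| 0.8 and 0.8 | 0.14 | 11.3% | 12.9% |
| 1.4 and 0.5 | 0.14 | 11.6% | 13.0% |
| 1.0 and 1.0 | 0.20 | 19.0% | 22.4% |
| 1.4 and 0.8 | 0.21 | 21.0% | 24.4% |
| 1.4 and 1.0 | 0.26 | 29.0% | 33.9% |
| 1.4 and 1.4 | 0.33 | 45.6% | 54.0% |

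Spearman gives no protection: 48.1% and 56.4% in the last row. The partial correlation given arm rejected in 4.9% to 5.2% of trials in every setting.

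**The case against.** The strongest reply is that the article never says the arms are pooled. Correlation within each arm, or in the exercise group alone, would fit both sections. This is a condensed article, and how an exploratory correlation is run is often left to a fuller plan. That stands as a limit: a reader might infer that a whole-sample analysis has been decided, and the text does not go that far. It does not dispose of the point. The article names the test, the rule for choosing between its two forms and the significance level, and the named test has no place for arm.

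A reader might also infer that the trial will present allocation as proof of mechanism. The text does not support that. It speaks of potential associations to be explored, makes no mediation claim, and states its aim in terms of sleep quality and OSA severity. The exploratory wording asked of such analyses is already there.

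Third, 54% might be taken as the plan's own expectation. It is not. It needs 1.4 SD on both variables, which rests on an assumed ρ of 0.5 and on an effect size tied to no named outcome; the outcomes labelled primary are the PSQI and the ESS. For neck circumference no exercise effect is stated, so inflation in those two of the six pairs has no basis in the document.

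Finally, a pooled test that rejects in these settings is detecting a real marginal correlation. That is correct: the error lies in reading it as a relation between participants beyond the effect of arm. The rates above should be understood in that sense.

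**Conclusion.** The point holds as a minor one. Section 2.10 fixes an unadjusted bivariate test at 0.05 and leaves the handling of arm open. One permitted reading, the plain one, lets the treatment effect appear as an association between changes; a within-arm analysis would not.

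Under pooling, the inflation runs from slight to large according to shifts that the article does not give, and it requires exercise to shift both variables. The article supports that condition for the pairs with VO2 and BMI. The calculation rests on normal change scores, equal variances and 1:1 arms. The analysis is exploratory, and no primary comparison depends on it.

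**What to change.** State in section 2.10, and refer to it from section 2.6.5, that the associations between changes are estimated conditional on arm. This can be a partial correlation given arm, or a linear model of the change in AHI or ODI on the change in the explanatory variable with arm as a covariate. Add scatter plots with the arms marked, and say that any pooled coefficient is descriptive only. Adjustment for arm alone cures the defect; a baseline covariate is optional and not needed for this purpose.

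The cost is one sentence, about one degree of freedom and probably smaller reported correlations. No further data or participants are needed.

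### Losses are promised a place in the intention-to-treat analysis, but the only comparison named, repeated-measures ANOVA, omits anyone without a post-test, and the adherence exclusion adds to the conflict

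*Protocol article*

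**What the plan says.** Three statements in the protocol article bear on this.

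- **Analysis sets.** Section 2.3 (Sample size) states: "Losses after randomization will be included in the intention-to-treat analysis but not in the analysis of the protocol". Section 2.10 (Data analysis) repeats the rule: "losses after randomization will be included in the intention-to-treat analysis but not in the analysis of the protocol". How losses are treated is therefore what separates the ITT analysis from the per-protocol analysis.
- **Method.** Section 2.10 states: "Repeated-measures ANOVA will be applied to assess post-intervention group-by-time interactions". The data will be "subjected to statistical analysis using the IBM SPSS 20.0 software". No other between-group comparison of outcomes over time is named, and the article mentions no imputation, no carry-forward rule and no mixed model.
- **Adherence.** Section 2.2 (Participants) says that those who do not reach 85% adherence to the interventions will also be excluded from the study. It does not limit this to the per-protocol analysis.

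On sample size, section 2.3 obtains 30 for the repeated-measures ANOVA and then says: "This number will be increased by 20% to account for potential sample losses", which gives 36, or 18 per group.

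**The concern.** Standard repeated-measures ANOVA in SPSS needs a value at every time point and deletes incomplete cases listwise. A participant who is lost and has no post-test cannot enter it. For such participants the stated method does not produce the stated analysis set, and the ITT and per-protocol results would both leave them out.

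The arms place unequal demands on participants. The exercise group has 36 sessions over 12 weeks (section 2.8), while the control group receives a booklet and remotely sent videos. If loss differs by arm and is related to outcome, a completer comparison is biased, and readers would meet it under an ITT label.

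The adherence rule makes this worse. If participants below 85% are removed from the study, people who could have been measured may become missing, and they are most likely to come from the arm with the heavier schedule.

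**Working it through.** **Inputs.** From section 2.3: α = 0.05, power 0.95, effect size 0.35 (read as Cohen's f), N = 30 raised by 20% to 36, 18 per group. From section 2.10: changes are defined as before versus after the intervention, so I take two time points (the design figure is not shown). Assumed, because the article does not give them: correlation between the two measurements ρ = 0.5 and sphericity 1.

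**1. The plan's own figure.** For the within-between interaction with m = 2 time points and k = 2 groups:

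λ = f² × N × m / (1 − ρ), df1 = (k − 1)(m − 1) = 1, df2 = (N − k)(m − 1) = N − 2.

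| N | λ | Power |
|---|---|---|
| 28 | 0.1225 × 28 × 2 / 0.5 = 13.72 | 0.946 |
| 30 | 0.1225 × 30 × 2 / 0.5 = 14.70 | 0.959 |
| 36 | 0.1225 × 36 × 2 / 0.5 = 17.64 | 0.983 |

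The smallest even N reaching 0.95 is 30, as stated. This depends on ρ: for ρ = 0, 0.3, 0.5 and 0.7 the required N is 56, 40, 30 and 20.

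**2. How many losses the plan allows for.** 30 × 1.2 = 36, and 36 − 30 = 6, which is 6/36 = 16.7% of those randomised. The plan therefore expects 30 participants with usable data, so the calculation treats losses as contributing nothing.

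**3. What the named test uses.** With two time points the group-by-time interaction compares the mean of (post − pre) between arms, so its F equals the squared two-sample t on change scores. I checked this on simulated data for 36 participants with 6 post-tests missing:

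- squared t on the 30 completers' changes: 12.775;
- interaction F from an ANOVA with subject effects, 30 completers only: 12.775 on 28 residual df;
- the same ANOVA with the 6 baseline-only records added: 12.775 on 28 residual df.

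Participants without a post-test add nothing, so the test uses 30 of 36.

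**4. Illustration of the stake, under an assumption the article does not make.** Suppose k of the 18 exercise participants are lost and gain nothing, no controls are lost, and completers gain δ over controls. The all-randomised difference is δ(18 − k)/18 and the completer difference is δ, so the completer result is too large by 18/(18 − k) − 1.

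| k lost of 18 | Overstatement |
|---|---|
| 3 | 20% |
| 4 | 29% |
| 5 | 38% |
| 6 | 50% |

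**5. The adherence threshold.** If adherence is counted over the 36 sessions, 31/36 = 86.1% passes and 30/36 = 83.3% does not. Six missed sessions are enough for exclusion under section 2.2, whereas sections 2.3 and 2.10 keep losses after randomisation in the ITT analysis.

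**The case against.** The strongest reply is that a journal article may leave its missing-data rule to a full protocol or analysis plan. ANOVA run on imputed data would satisfy both sentences, and the promise to include losses may imply such a step. This stands in part. A reader might infer that the final ITT result is bound to be a completer analysis, and the article does not support that. What remains is that two stated elements, an analysis set and a method, do not fit together as published. That is more than a missing detail.

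Second, the article does not define losses. Someone who stops training but returns for the post-test has both values and can enter the ANOVA. This stands: the conflict concerns only participants without a post-test.

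Third, a reader might apply 20% to 36 and conclude that 7.2 participants disappear, leaving about 29. Section 2.3 applies the 20% to 30, so the plan's own allowance is 6 lost and 30 remaining.

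Fourth, the article gives no loss by arm and no link between loss and symptoms. This stands too. Bias is a risk here and has not been shown; the 20% to 50% range follows only from the assumption stated with it.

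Finally, a mixed model with two visits does not correct loss driven by symptoms that arise after baseline and are never recorded. This is correct, and it is why a sensitivity analysis belongs in the remedy.

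**Conclusion.** The point holds in limited form. Unless imputation is applied, the ITT result will omit every participant without a post-test. That is up to 6 of 36 under the plan's allowance, and only if all losses lack a post-test. The conclusion rests on one pre-test and one post-test and on the standard listwise handling of repeated-measures ANOVA.

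The adherence exclusion in section 2.2 contradicts the ITT statement on the face of the text, whatever the missing-data method, and the passages must be reconciled.

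A reader should not conclude that the trial is underpowered for this reason: with ρ = 0.5, power is about 0.96 with 30 completers. Nor is the sample size itself in error on this point. The consequences are possible bias of unknown size and an ITT label that the named method does not earn for those without a post-test.

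**What to change.** 1. **ITT model.** Replace repeated-measures ANOVA for the ITT set with a likelihood-based linear mixed model on all randomised participants, with a common baseline, an arm-by-time effect, and the randomisation strata (sex and OSA severity). An acceptable alternative is ANCOVA adjusted for baseline and strata after multiple imputation, with arm, baseline, strata and, if wanted, sessions attended in the imputation model.
2. **Sensitivity analysis.** Add one analysis that imputes missing exercise-arm values from the control arm. The main model is valid only if loss is explained by baseline, arm and strata (plus attendance, if used in the imputation).
3. **Adherence rule.** Reconcile section 2.2 with sections 2.3 and 2.10: participants below 85% adherence are still measured and stay in the ITT set, and the threshold defines the per-protocol set only.
4. **Per-protocol set.** Keep the complete-case analysis there, and label it as such.

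The cost is revised wording and a little more analysis work, all possible in SPSS, with no extra participants or planned visits. Baseline-only participants add little precision, so the benefit lies in validity under a stated assumption and in an accurate label.
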